**Figure 3. Information safety processing diagram**

### ***User Interface and User Experience Design***

The user interface should be designed to be friendly and efficient, which is the key to improving users' experience in utilizing and engaging with the app. Our team has designed a human-centered app by following the principle of a friendly and efficient user interface with thorough consideration of users' needs and characteristics.

First, the user interface and user experience design should reflect users' mental models. As our target users are professionals, including doctors from village clinics and from township and county-level hospitals as well, the design of the interface took full account of their respective needs and expectations as well as limitations. In line with the results from the contextual research, we assessed the users' proficiency in using smartphones by choosing an extensively used app as a benchmark. Considering that county and town hospital doctors are already familiar with Web-based health care information system, we adopted similar structure design and visual styles.

Second, the design should improve workflow efficiency, avoid information-entry errors, and provide smooth app access for users. Therefore, we designed simple and easily recognizable icons, such as contrasting colors for positive and negative information and distinctive graphical shapes to indicate different click status, to quickly draw users' attention and help them understand the information effectively. In addition, we used uniform marks for navigation to make the transition and interaction of different interfaces clear and consistent. Designing with specific blocks to distinguish information contents and prefilling with defaults also improved the usability and reduced the chance of entry errors.

### ***Step 4: Pilot Testing and Agile Development***

Following the above studies, we then developed a fully functional app prototype, which was used for discussion in the multidisciplinary workshop as well as for demonstration to and

interviews with the village doctors. On the basis of their feedback, we carried out the first round of iterative design and developed a testing version for the pilot study.

The pilot study was conducted in 4 rural villages of Nanhe County for 3 months. During the pilot study, each village doctor was provided with an Android phone with the app installed to implement the SINEMA intervention model. Each village doctor was asked to care for about 10 patients in his or her village. In-depth interviews with all the village doctors and township physicians were conducted after the pilot study to collect any feedback about the usability of the app and suggestions to optimize the app.

On the basis of the feedback from the end users, we conducted several rounds of revision of the app. During the process of development, we took advantage of the latest technologies to speed up the iteration, for example, the online tracking and positioning of bugs for rapid and efficient feedback and the hotfix technology for repairing and updating the app without releasing a new version of the app for village doctors.

*Step 5: Main Trial and Users' Follow-Up Survey*

The finalized app system was utilized to support the implementation of the SINEMA model. **Figure 4** shows the screenshot of the key functions of the SINEMA App for three different types of stakeholders. A follow-up survey will be conducted to all users to understand their using experience of the SINEMA App.

[figure not shown]

**Figure 4. Screenshot of Key Functions of the SINEMA App**

#### 4.2.2 Development of the voice message dispatching system

We used multiple methodologies, including literature review, expert consultation, qualitative in-depth interviews, and field-based pilot study followed by surveys and interviews, in developing the messages to ensure that the message contents were built based on research evidence and in line with the clinical guidelines and were suitable for the local context. The development process for the mobile phone message banks consisted of the following 5 stages: (1) conducting a literature review on existing message banks targeting people with stroke, (2) interviewing stakeholders to identify the needs of stroke patients, (3) creating and designing the message contents and message sending algorithm, (4) conducting pilot testing of the messages among patients in 4 villages, and (5) refining and finalizing the message bank and sending algorithm based on the lessons learned from the pilot study. **Figure 5** outlines the design process.

[figure not shown]

**Figure 5. Overview of key stages of message development.**

##### *Stage 1. Literature Review on Existing Message Banks*

To assist the design of the message bank, we conducted a literature review based on the PubMed database to search for existing text message banks published between October 1, 2011, and October 1, 2016. Our own design of the messages began in November 2016. Key search terms included stroke and text messages. A total of 2 reviewers screened the searched papers, and a snowball review by reviewing titles and abstracts of references of searched papers was also conducted to increase the scope of the review. Existing message banks were extracted and translated into Chinese as a reference for the design.

##### *Stage 2. Contextual Research*

To identify the needs of stroke patients, we visited the field 3 times over the period of 5 months from May to September 2016 and conducted in-depth interviews among stakeholders, including

stroke patients and family caregivers. Semi-structured interview guides were developed, and questions in the interview included patients' health status and needs for managing their conditions. Stroke patients were identified with the assistance of village doctors with the criteria that the participants were aged 18 years or older, had a history of stroke diagnosed at the county- or higher-level hospitals, were in clinically stable condition, had basic communication abilities, and were willing to participate in the study. Stroke patients' family members who were at home while the research team visited and were willing to participate were also interviewed separately. The number of participants interviewed was determined based on the saturation theory, whereby participants were recruited until no further new information was acquired through the interview process.

### *Stage 3. Design of Message Content and Message Sending Algorithm*

We designed the contents of messages on the basis of the existing message banks from the literature review, the identified needs of stroke patients from contextual research, and the behavior change theories such as the health belief model and the transtheoretical model. First, the structure and focus of the message bank were identified so that messages could tap into key dimensions based on patients' needs. We then grouped the existing messages into 6 categories based on their contents, including management of metabolic risk factors, medication adherence, tobacco and alcohol control, dietary change, exercise and rehabilitation, and psychological support. The content of the messages was modified to be suitable for stroke patients in rural China. The messages were then verified by stroke specialists working in tertiary hospitals and recorded in the local dialect.

We also designed the message dispatching algorithm by setting the sending time and frequency based on the daily habits of stroke patients. This algorithm was linked with a digital health management system that was designed to support the delivery of the digital health components of SINEMA intervention.

### *Stage 4. Pilot Study*

A pilot study was conducted in 4 villages to test the SINEMA intervention model, including the acceptance of the message-based intervention among stroke patients. Participants who were aged older than 18 years, had a history of stroke but in a clinically stable condition, and able to communicate via mobile phone were eligible to participate in the study. In each village, village doctors screened stroke patients in their villages and provided the list to the study team. Participants were invited by village doctors and recruited by the research team. Before the commencement of the pilot study, a structured questionnaire, including questions on participants' demographic characteristics and disease history, designed based on previous studies, was administered by the research team through face-to-face interviews.

During the 3-month pilot study, participants and their caregivers received text messages at 3 pm every 2 days, and the participants also received voice messages with the same content at 7 pm on alternating days when they did not receive the text messages. At the end of the pilot study, participants completed a short questionnaire administered by their village doctors. Questions in the survey included whether they had read or listened to the messages, their understanding of the contents of the messages, and their perspectives on the helpfulness of these messages. In-depth interviews were also conducted by the research team among selected participants to seek detailed feedback.

### *Stage 5. Refinement of the Messages*

After the pilot study, the research team summarized the feedback from participants and refined the message contents and message dispatching algorithm. To optimize the acceptance and understanding of the messages, the research team revised the language in each message based on participants' feedback and preference. Village doctors and physicians from county hospitals were invited to verify the messages to ensure that local contexts were taken into full consideration, and the terms used in the messages were understandable by the target population.

## **4.3 Pilot study**

To evaluate and optimize the SINEMA model and its procedure before the main trial, a four-week pilot trial was conducted in four villages for three months.

### **4.3.1 Study population and baseline survey**

The four villages were selected from two townships of the five villages for the main trial. The villages selected for the pilot trial will not be used for the main trial. In each pilot village, about 10-15 patients were recruited using the same criteria as planned for main trial. Participants also completed the baseline survey as a pilot for the survey.

### **4.3.2 Pilot study procedure**

In each village, all participants recruited receive the SINEMA intervention. Village doctors who were involved in the pilot study received training and were provided with a testing version of the SINEMA App. Participants received the SINEMA intervention including monthly follow-up, daily text-messages and voice-messages and some of their family members also received text-messages. The intervention lasted for three months.

### **4.3.3 Evaluation and finalization**

After the pilot intervention, four village doctors, eight patients who received intervention, two township-level managers and one county-level manager were invited to participate in an in-depth interview to provide feedback. Fifty-five participants completed a survey to provide feedback about the SINEMA intervention. The contents and delivery approach of the SINEMA intervention was optimized and finalized based on the pilot study findings before the trial.

After testing the feasibility of the SINEMA model in a 3-month pilot study conducted in 4 villages, we modified and finalized the SINEMA model to target blood pressure control, medication adherence, and physical activity. The SINEMA model (**Figure 6**), cognizant of health system's organization around primary, secondary and tertiary healthcare levels in China, adopts the principles of cascade training with feedback and task-sharing, and relies on existing human resources available at the community level. It also proposes the use of innovative mobile technology as tools (in the form of an Android-based SINEMA APP for village doctors and cellphone voice messages for participants). The overarching aim is to strengthen the capacity of village doctors on delivering services for the secondary prevention of stroke and promoting medication adherence and physical activity among stroke survivors.

[figure not shown]

Figure 6. Graphic figure to illustrate SINEMA intervention

## 5. STUDY DESIGN OF THE SINEMA TRIAL

The SINEMA trial is a cluster randomized controlled trial to evaluate the effectiveness of a system-integrated technology-enabled model of care to improve the secondary prevention of stroke in Nanhe County, a rural area of Hebei Province, China. Fifty villages from 5 townships are stratified randomized in a 1:1 ratio to either the intervention arm (implementing SINEMA model) or the control arm (usual care). The trial duration for each participant is 1 year. **Figure 7** shows the basic design of the trial flow chart.

[figure not shown]

**Figure 7. The design of the SINEMA Trial**

## 5.1 Study site

This study is conducted in Nanhe County, a county in Hebei Province, China, with an intention to generate solutions that can be adapted in other resource-limited settings. Nanhe County is located on the stroke belt of China, an area marked with a comparatively high prevalence of stroke. It is a “provincial poverty county” with an annual disposable income per capita as 11,030 RMB (less than half of the average national annual disposable income per capita). In Nanhe County, there are 2 county-level hospitals, 8 township hospitals and 218 village clinics (one for each village). The capacity of these healthcare facilities is relatively limited, and the health system is fragmented across primary, secondary and tertiary healthcare facilities. Most stroke patients receive acute care in hospitals equivalent or above county level when they have urgent stroke events. Follow-up care after hospital discharge is minimal to none-existent. Access to the Internet, nevertheless, is widespread, and cell phone (including both feature phone and smartphone) ownership among adults is high (>90%). A survey conducted among rural residents in Hebei Province found that 94.7% participants owning a mobile phone and about half of them surf the internet through the mobile phone.

## 5.2 Study population

### 5.2.1 Selection of township and villages

We will select 5 out of the 8 townships of Nanhe County based on their demographic and economic conditions, and township leaders’ willingness to participate in our study. The top 5 townships where there are the greatest number of the villages with a minimum population size of 1500 were selected to participate in the study. In each township, we will select 12 villages

from each township as eligible villages where the number of population ranks at the top with a minimum population size of 1500. In each village, we will ask village doctors to screen the stroke survivors in their villages based on health records and their best knowledge and generate a list of potential participants. To reach the targeted sample size, we will recruited 10 villages from each township according to the number of stroke survivors screened and village doctors' willing to participate in the study.

#### 5.2.2 Selection of village doctors.

For each village, 1 village doctor will be selected who is an officially certified village doctor and can stay in the village for at least 4 days per week in the next 12 months, as well as knows how to use a smartphone and agrees to participate in the study. If there is more than 1 eligible village doctor in the village, the leader of the village clinics will be selected.

#### 5.2.3 Recruitment of participants.

Stroke survivors meeting the following criteria will be recruited to form the study sample: those who are over 18 years old, have a history of stroke (including ischemic and hemorrhagic stroke) diagnosed at county hospital or higher-level facilities, are currently in a clinically stable condition and not receiving acute stroke treatment, will live in this village for at least 9 months during the next 12 months, have basic communication ability (i.e. can understand simple instructions) and give their informed consent. Exclusion criteria are: patients who are unable to get out of bed without maximum assistance, have serious life-threatening disease such as cancers or an expected life span of less than 6 months.

The recruitment will be conducted village by village. Eligible stroke patients will be invited to participate in the study by village doctors. If there are less than 30 screened stroke survivors in the village, all screened stroke survivors were invited. If there are more than 30 screened stroke survivors, 30 stroke survivors are randomly selected and invited by village doctors. Recruitment is conducted by trained research staffs in the village clinics. All patients will be informed and provided written consents before participating in the study.

### 5.3 Sample size

Based on a sample of 1,250 prevalent stroke patients in 50 villages (with 25 villages per arm and on average 25 patients per village), assuming loss of 2 clusters (villages) per arm and loss of 1 patient per village on average, an intra-cluster correlation coefficient (ICC) of 0.04 (a conservative assumption), and a standard deviation (SD) for SBP pre-post change of 20 mmHg, the study has 83% power (with 2-sided alpha = 0.05) to detect a 5 mmHg net difference in pre-post change of SBP between intervention and usual care arms. Previous studies have been demonstrated that a 5mmHg difference is a meaningful change for stroke recurrence in 3-5 years. The effect size of a 5mmHg difference corresponds to a standardized effect size of 0.25 (5/20) and therefore we will have more than 80% power to detect such standardized effect sizes for secondary outcomes of interest, assuming the same level of clustering of those outcomes.

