Patients' awareness and health behaviors also contribute to the suboptimal secondary prevention of stroke in rural China. With rapid urbanization, rural communities in China are left behind with large number of older people who are vulnerable. They have relatively poor health conditions and receive limited insurance protection through the China's New Cooperative Medical Scheme. Lacking awareness of the self-management of chronic conditions and economic difficulties result in poor adherence to secondary prevention. The PURE China study compared cardiovascular patients in urban and rural communities and found that the adherence to healthy lifestyles and the use of secondary prevention drugs are lower among cardiovascular patients in rural communities than in urban settings in all regions with different economic development levels. A study based on the China National Stroke Registry also showed that only 46.2% of the stroke patients continue the use of prescribed secondary prevention drugs after 3 months post hospital-discharge, and the persistence of use was positively associated with younger age, higher family income and the hospitals where the patients received treatment.

Mobile health (mHealth) technologies, in the form of text messaging and mobile applications, have emerged as a promising approach to support behavior change among both the providers and patients. Studies showed that mHealth technologies can empower patients' self-management of chronic conditions, increase access to healthcare services for vulnerable population, enhance communication flow, and improve the delivery of training to healthcare workers. However, despite the ubiquitous mobile network coverage and high penetration rate of mobile phones, few mHealth interventions have been implemented in rural China. The feasibility and effectiveness of such interventions is worthy of investigation.

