## 5.7 Outcome evaluation

The primary outcome is systolic blood pressure (SBP) of participants. The effectiveness of the program will be evaluated by the SBP at 1-year follow-up between the intervention and the control arm. Blood pressure is measured on the right upper arm (or left arm if the right arm is disabled) with participant seated after 5 minutes of rest using an electronic blood pressure monitor (Omron HEM-7052). Two measurements are taken, and the mean value is calculated. If the differences between the 2 SBP is larger than 10 mmHg, a third measurement is conducted, and the mean value of the only or the last 2 reading is calculated.

Secondary outcomes include participants' diastolic blood pressure, mobility, medication adherence, physical activity level and quality of life. Mobility is measured using the Timed Up and Go test, a simple and quick functional mobility test that requires the participants to stand up, walk 3 meters, turn, walk back, and sit down. Medication adherence is measured using the 4item Morisky Green Levine Scale with scores ranging from 0 to 4 with a higher score indicating lower medication adherence. Participants will respond to the 4 questions with yes or no for each type of medicines (antihypertension, aspirin and statin) if they were prescribed by the physicians before. Physical activity level is measured using the short version of the International Physical Activity Questionnaire (IPAQ). Participants were asked to recall the frequency and duration of rigorous activities, moderate activities and walking they performed in the past 7 days. Quality of life is measured using EuroQoL- 5 Dimensions-5L (EQ5D).

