| Medication adherence | 
Self-reported medical adherence is measured by Morisky Green Levine Scale separately for anti-hypertensive medicine, aspirin and statins if the participant was taking the medicine. A score ranged from 0 to 4 are calculated by summing all coded answers where lower scores correspond to better medication adherence.
                                                                                                                                                                                                                                                                                                                                                                                                                                                              | The variable will be dichotomized as high adherence (0) vs. low to medium adherence (1-4).             |

---

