### 1026 7.3.2 Secondary effectiveness analyses of binary outcomes

1027 Medication use, adherence, and physical activity levels are pre-specified binary outcomes. We  
1028 will analyze these variables using the generalized estimating equations (GEE) approach to  
1029 obtain population-averaged intervention effects. As with the primary analysis approach, strata  
1030 will be included as fixed effects in the model. In contrast to using random intercepts in the linear  
1031 mixed models used for the primary and continuous secondary outcomes, a working correlation  
1032 matrix will be used to account for clustering. More specifically, the modified Poisson GEE  
1033 approach (with log-link) will be used to obtain probability ratios (often referred to as risk ratios).  
1034 Although we expect to see correlation of outcomes within clusters, an independent working  
1035 correlation matrix will be used rather than exchangeable as it may provide greater stability with  
1036 the anticipated variability in cluster size. Robust standard errors will be used to account for  
1037 potential model misspecification. Importantly, because adherence can only be measured in

those who are taking medications, it will be important to determine the validity of a between-arm comparison. To this end, we will compare the predictors of medication use in each arm, for each of the three medications, thereby evaluating whether there is good internal validity of the comparison. In the case that we identify differences between arms in characteristics of those taking medications, we will adjust for such characteristics in the regression model.

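### The claim of more than 80% power for secondary outcomes does not extend to medication adherence, which is analysed drug by drug in a subset, unless about 84% or more of participants take the drug

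*Combined protocol and SAP*

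**What the plan says.** Section 5.3 plans as follows: "Based on a sample of 1,250 prevalent stroke patients in 50 villages", "with 25 villages per arm and on average 25 patients per village". It continues by "assuming loss of 2 clusters (villages) per arm and loss of 1 patient per village on average", which leaves 23 villages of 24 patients, or 552 patients, per arm. With an ICC of 0.04, an SD of 20 mmHg and a two-sided 5% test, it reports 83% power for 5 mmHg. It restates this effect as 0.25 SD and concludes: "therefore we will have more than 80% power to detect such standardized effect sizes for secondary outcomes of interest". The only condition attached is that the other outcomes cluster to the same degree.

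Section 5.7 lists the secondary outcomes as "diastolic blood pressure, mobility, medication adherence, physical activity level and quality of life". Table 4 scores adherence "separately for anti-hypertensive medicine, aspirin and statins if the participant was taking the medicine". Section 7.3.2 (binary outcomes) gives the same restriction, "because adherence can only be measured in" people who are on the medication. Section 5.7 puts the adherence questions for each drug to those who had been prescribed it, which is a different denominator but also a subset.

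The plan states no expected share of takers for any of the three drugs and no separate power for adherence.

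**The concern.** Carrying power from the primary to a secondary outcome at the same standardized effect requires the same clustering and also the same number of analysed patients. Section 5.3 states the first condition and omits the second. Adherence cannot meet the second unless everyone takes the drug in question.

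Adherence is one of the five secondary outcomes in 5.7, supplies three binary comparisons (one per drug), and is one of the three targets of the finalized model in 4.3.3. A reader who takes 5.3 at face value would think each comparison has less than a 20% chance of missing a 0.25 SD effect. For a drug used by a minority of participants that chance is considerably larger, and a null result would look more informative than it is.

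**Working it through.** **Inputs.** All are from 5.3 unless noted: k = 23 villages per arm and m = 24 patients per village after losses; ICC = 0.04; d = 5/20 = 0.25; two-sided alpha 0.05. The share of participants taking a drug, s, is not given in the documents and is varied.

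**Formulas.** Design effect DE = 1 + (m − 1) × ICC. Effective n per arm = k × m / DE. Noncentrality = d × √(effective n / 2). Power is from the noncentral t with 2k − 2 = 44 df.

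**Reproducing the plan's figure.** DE = 1 + 23 × 0.04 = 1.92. Effective n = 552 / 1.92 = 287.5. Noncentrality = 0.25 × √143.75 = 3.00. Power = 83.4%, which matches the printed 83%. A normal approximation gives 85.0%, so a cluster-level t calculation is the likely source.

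**Adherence.** Replace m by 24 × s and change nothing else. The design effect falls with the smaller number per village, so that benefit is already counted.

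| Share taking the drug | Patients per village | DE | Effective n per arm | Power at 0.25 SD | Effect with 80% power |
|---|---|---|---|---|---|
| 100% | 24.0 | 1.92 | 287.5 | 83.4% | 0.24 SD |
| 80% | 19.2 | 1.73 | 255.6 | 78.9% | 0.25 SD |
| 60% | 14.4 | 1.54 | 215.6 | 71.9% | 0.28 SD |
| 46.2% | 11.1 | 1.40 | 181.7 | 64.5% | 0.30 SD |
| 30% | 7.2 | 1.25 | 132.7 | 51.3% | 0.35 SD |
| 20% | 4.8 | 1.15 | 95.8 | 39.5% | 0.41 SD |

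The 46.2% row is illustrative. The Background cites a registry study in which "only 46.2% of the stroke patients continue the use of prescribed secondary prevention drugs after 3 months post hospital-discharge".

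**Break-even.** Power reaches 80% at s = 84%. With no loss (25 villages × 25 patients, 48 df), full-sample power is 87.1%, break-even is 69%, and power at 46.2% use is 69.4%.

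**Sensitivity.**
- Removing 4 df for the township terms changes power by about 0.2 percentage points.
- On a binary scale with Cohen's h = 0.25 (for example 50% against 62.4%), the normal approximation gives 85% for the full sample and 66% at 46.2% use, so the result does not depend on treating the outcome as continuous.
- With ICC = 0, power at 46.2% use is 78.8%.
- Uneven numbers of takers per village, not modelled here, would lower power further.

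**The case against.** **The 46.2% is not the input needed.** It describes persistence with prescribed drugs three months after discharge in a national registry. It is not the share of this trial's long-standing survivors taking a given drug at 12 months. This stands. A reader might infer that adherence power is 65%, or that the plan expects low use of each drug; the documents support neither.

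**The trial did better than its assumed losses.** Part B, 3.1 reports 1,266 survivors assessed at 12 months, against the 2 × 552 = 1,104 behind the 83%. If all 50 villages were kept (an assumption), that is 1,266 / 50 = 25.3 per village. Full-sample power is then 87%, with 77% at 60% use, 70% at 46.2% and 81% at 70%; break-even is about 68%. Section 5.3 also calls its ICC conservative. If it were 0.02 (an assumption), the same sample would give 77% at 46.2% use and 85% at 60%. This also stands: a shortfall for all three drugs is not established. It does not rescue a little-used drug: at 20% use and ICC 0.04, power is 44% even with 1,266 patients.

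**The prescribed-patient denominator in 5.7 may be larger than current takers.** True, but it is still a subset, and the two definitions need reconciling anyway.

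**Consequences are limited.** Section 7.1.2 promises 95% confidence intervals and ties the 5% significance test to the primary outcome only; Table 4 also has medication use, a full-sample outcome, for each drug; and the active phase ended in July 2018. Intervals will show the imprecision, and the design can no longer change. None of this makes the power sentence correct as written.

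**Conclusion.** The concern holds in conditional form. Section 5.3 extends its power to secondary outcomes without allowing for a smaller analysed sample, and medication adherence always has one. With the plan's inputs, the claim fails for any drug taken by fewer than about 84% of participants, or about 69% with no loss. This rests on equal village sizes, an ICC of 0.04 among takers and a 0.25 SD effect.

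How far power falls for each drug is unknown, because no use rate is stated. The point does not touch the 83% for the primary outcome, which reproduces, nor the secondary outcomes measured in everyone. It is also separate from whether comparing takers between arms is valid, which 7.3.2 addresses.

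**What to change.** In 5.3, limit the statement of more than 80% power to secondary outcomes measured in all participants, such as diastolic blood pressure, physical activity, quality of life and medication use. For adherence, add a sentence giving the break-even use (about 84% with the planned losses, about 69% with none) and the power over a range of shares taking each drug: about 79% at 80% use, 72% at 60%, 64% at 46% and 39% at 20%. The detectable effects at 60%, 46% and 20% use (about 0.28, 0.30 and 0.41 SD) could be given instead. Say that the range is used because no per-drug rate was available. Settle in the same edit whether the denominator is those prescribed the drug (5.7) or those taking it (Table 4, 7.3.2).

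The cost is one or two sentences, with no added patients, data or analyses. The downside is a less favourable stated power for one secondary outcome. With the trial over, the value lies in how the adherence results are reported and read.
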